### Follow-up clinic visits

All caregivers and study participants are requested to return to a specific study site for a follow-up visit at 2, 4, 8 and 12 weeks post inclusion. Those receiving LNS are also requested to return at 6 and 10 weeks post inclusion to restock sachets.

At follow-up clinics child anthropometrics are measured, a clinical review is done and inquiries are made into LNS compliance (if relevant). At week 12, additional parameters are measured; blood and stool samples are collected and bioimpedance and child development are assessed and a discharge questionnaire is completed. An overview of the measurements taken at each time point are provided in figure 4.

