| **Criteria for inclusion:**   - Age 12 - 59 months - HAZ < -2 according to WHO growth standards (2006) - Care-taker able and willing to return for follow-up visits and agrees to phone follow-up - Living within the catchment area - Written informed consent given by parent/caregiver   **Criteria for exclusion:**   - SAM, defined as MUAC <115 mm OR WHZ<-3 OR bipedal pitting oedema - Medical complications requiring hospitalization. - Obvious disability that impedes eating capacity - Disability that makes length/height assessment problematic - Participation in another study which impacts on this study or previous enrollment in this study. - Family plans to move away from the catchment area in the next 6 months. - History or known allergy to peanuts or milk | |
| **Intervention:**  A supplementary food intervention. Of the 750 children included in the study, 600 are randomly allocated to one of four LNS-LQ upon inclusion and 150 are randomly allocated to no supplementation. All children receive nutrition counselling at inclusion. Those randomised to LNS are given one sachet of 100g per day in addition to the home based diet. Each 100g LNS-LQ sachet provides approximately 530kcal, provides up to half of the average daily energy requirements, and satisfies most of the estimated daily micronutrient requirements (age dependent). | |
| **Duration of intervention:**  12 week intervention. | |
| **Data collection and follow-up**  **[figure not shown]** | |
| **Figure 2:** Study design framework and time-points for data collection.  The 750 children with a HAZ <-2 are included and randomly allocated to one of four LNS-LQ or to a reference group. Supplemented children are provided one LNS-LQ sachet per day (in two-week allocations) over a period of 12 weeks. After inclusion, all children, irrespective of allocation are followed-up every 2-4 weeks until 12 weeks. | **[figure not shown]** |
| **Statistical Methods:**  Primary, secondary, and tertiary endpoints are analysed by means of longitudinal data analysis since repeated measurements are recorded per patient. | |

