## Tertiary outcomes

Blood hormone markers

- Insulin-like Growth Factor-1 (IGF-1)
- Insulin

Blood markers of systemic inflammation

- C-reactive protein (CRP)
- Alpha-1-acid glycoprotein (AGP)

Blood markers of enteric function

- Citrulline.
- Blood markers of micronutrients status Iron (ferritin and soluble transferrin receptor)
- Vitamin B12
- Folate
- Vitamin A (retinol binding protein)
- Stool markers of intestinal inflammation Myeloperoxidase (MPO)
- Neopterin (NEO)
- Alpha-1-antitrypsin (AAT)

Gut microbiota

Safety, morbidity and loss to follow-up

- Proportion deteriorated to MAM, measured as WHZ ≤ -2 and >-3 or MUAC ≤ 125 and >115mm) and proportion deteriorated to SAM, measured as WHZ <-3, MUAC <115mm or presence of nutritional oedema.
- Proportion of participants who die during the study period (mortality)
- Number of morbidity episodes, duration and severity (diarrhea, pneumonia, fever, malaria, other) during the intervention period
- Proportion lost to follow-up during the study period

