### Child anthropometry

The following anthropometrics are taken at baseline, week 2, 4, 8 and 12 weeks; knee-heel length, MUAC, weight, height, skin folds (subscapular and triceps). The distance between the heel and knee is measured using a digital hand-held knemometer (Michaelsen KM et al, 1991). Knee-heel length is a sensitive measure of change in growth over short time periods, detecting smaller differences with less variation than overall height. Weight is measured using an electronic scale with a double weighing function. Height (measured in children 24 months and older) and length (measured in children <24 months) are taken using a standard wooden height/length board. The anthropometric indices HAZ, WAZ and WHZ are used to monitor nutritional status over time according to the WHO growth standards. Mid-upper-arm circumference is measured using a MUAC tape. A low MUAC has been associated with higher mortality risk in young children [29]. The MUAC has a high specificity and gives an indication of wasting and of lean mass accretion over time. Skin fold thickness is measured in the triceps and subscapular using a Harpenden skinfold caliper. Head circumference is measured using a non-stretch measuring tape at baseline, week 12 and week 24. Head circumference can be useful when interpreting child development outcomes.

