## Adverse events

In this trial, an adverse event constitutes any untoward medical occurrence in the clinical trial subject at any dose of the LNS nutritional intervention product and which does not necessarily have a causal relationship with this treatment. The AEs will be recorded in the CRF.

- All reported or observed adverse events (AEs) taking place during the intervention period of the trial will be recorded; this is from the time informed consent is given, until the time when the participant is discharged from the study.
- The PI will report all AE records to the sponsor biannually. The sponsor will keep detailed records of adverse events.
- AEs will be reported to SOMREC in the annual progress reports.

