## Compensation/Reimbursement

Participation in the study is free of charge and caregivers do not receive any payments for participation in the study. Caregivers will be reimbursed for their transportation costs which will include a small amount to cover the costs of food purchase during the day of the clinic visit. A maximum of 20,000UGX will be given per return trip. Caregivers who do not receive LNS-LQ supplementation for their child during the study will still receive the same opportunities for medical review. In addition, a small token of appreciation, worth not more than 10,000 UGX will be provided to families of unsupplemented children.

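### Supplemented families have two scheduled site contacts that reference families lack, so illness and non-serious adverse events can be captured more often in the supplemented arms

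*Protocol*

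**What the plan says.** **Visits.** Under Follow-up clinic visits (protocol section 10), all families are asked to "return to a specific study site for a follow-up visit at 2, 4, 8 and 12 weeks post inclusion". The next sentence applies to supplemented families only: "Those receiving LNS are also requested to return at 6 and 10 weeks post inclusion to restock sachets".

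**What is done at visits.** The same section places anthropometry and a clinical review at the follow-up clinics. Child anthropometry (section 22) sets one schedule for every arm: "The following anthropometrics are taken at baseline, week 2, 4, 8 and 12 weeks; knee-heel length, MUAC, weight, height, skin folds". Clinical examination (section 22) adds that the review covers recent medical history, without giving a recall period.

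**Restocking.** Section 16 says that staff ask about adherence when sachets are collected and names no other enquiry there. Product distribution (section 20) separates distribution from other operations and keeps distributors out of clinic data collection.

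**Adverse events.** Section 26: "All reported or observed adverse events (AEs) taking place during the intervention period of the trial will be recorded", running from consent to discharge.

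**Morbidity outcome.** Section 17 lists, among the tertiary outcomes: "Number of morbidity episodes, duration and severity (diarrhea, pneumonia, fever, malaria, other) during the intervention period".

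**Phone calls.** The Figure 4 legend (section 19) gives phone follow-up no fixed time points. Phone call follow-up (section 22) ties calls to appointments and covers illness, milk consumption, stool samples and, where it applies, adherence.

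**Comparison.** Section 18 plans a secondary analysis of 600 supplemented against 150 unsupplemented children.

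**The concern.** From week 4 to week 12 a supplemented family meets study staff every two weeks and a reference family every four. Adverse event capture is not tied to the common visits, so an illness mentioned at a restocking contact enters the record. A reference family with the same illness has no matching occasion to mention it. A question about why sachets were left uneaten may itself bring up illness; that is inference, but a natural one.

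At stake is the reading of morbidity and non-serious adverse events between supplemented and unsupplemented children. Extra capture in the supplemented arms pushes their counts up. That could hide a reduction in illness or look like a small excess. Reference families also know that they receive no supplement (Blinding, section 20), so masking does not protect reporting in this contrast.

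**Working it through.** **1. The planned comparison.** The stated detectable difference reproduces. With 10% loss, 600 and 150 become 540 and 135, and (1.960 + 0.842) × √(1/540 + 1/135) = 0.270 SD, or 4.88 mm with an SD of 18.1 mm. The protocol gives 0.27 SD and 4.9 mm. The figure concerns growth and says nothing about capture of illness, so the rest is a count of contacts.

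**2. Scheduled contacts after baseline.**

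| | Supplemented | Reference | Ratio |
|---|---|---|---|
| Site attendances | 6 (weeks 2, 4, 6, 8, 10, 12) | 4 (weeks 2, 4, 8, 12) | 1.5 |
| Anthropometry | 4 | 4 | 1.0 |
| Clinical review | 4 | 4 | 1.0 |

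**3. Illness time covered.** Suppose a caregiver reports illness from the last *w* weeks at each contact where illness comes up. Weeks covered = sum over contacts of min(*w*, weeks since the previous contact). The value of *w* is an assumption, since the protocol gives no recall period. Phone calls and the exercise book are left out because their yield is not stated.

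Reference intervals are 2, 2, 4 and 4 weeks. Supplemented intervals are six of 2 weeks if illness is also captured at weeks 6 and 10.

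| Recall *w* | Supplemented | Reference | Ratio |
|---|---|---|---|
| 1 week | 6 × 1 = 6 | 1+1+1+1 = 4 | 1.5 |
| 2 weeks | 6 × 2 = 12 | 2+2+2+2 = 8 | 1.5 |
| 3 weeks | 6 × 2 = 12 | 2+2+3+3 = 10 | 1.2 |
| 4 weeks | 6 × 2 = 12 | 2+2+4+4 = 12 | 1.0 |

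If illness is captured only at the common visits, both arms have intervals 2, 2, 4 and 4, and the ratio is 1.0 for every *w*.

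**4. Partial capture.** Nothing schedules illness questions at restocking, so capture there would probably be partial. With 2-week recall and a fraction *p* of the illness in the four extra weeks coming to light, the ratio is (8 + 4*p*)/8 = 1 + 0.5*p*. It is 1.0 at *p* = 0, 1.25 at *p* = 0.5 and 1.5 at *p* = 1. This assumes a constant illness rate that is equal in the two groups.

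**The case against.** The strongest reply is that everything scheduled is already equal. Weeks 6 and 10 are for restocking, clinical review belongs to the common visits, distributors collect no clinic data, and the only enquiry named at sachet collection is adherence. Phone calls about illness are open to all arms, and every caregiver receives an exercise book for noting illness treated elsewhere. Which reports enter an analysis is ordinary SAP content, and the SAP is not shown; nor are Figure 4 and the SOPs.

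Much of this stands, and it rules out several stronger readings:

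- *Deterioration to MAM or SAM is measured on unequal schedules.* It is not. The definitions rest on anthropometry or oedema, and anthropometry is scheduled 4 v 4. Only a chance observation, such as oedema noticed at restocking, could differ.
- *The Summary is contradicted.* It says "After inclusion, all children, irrespective of allocation are followed-up every 2-4 weeks until 12 weeks". Reference intervals of 2, 2, 4 and 4 weeks fit that.
- *The promise under Compensation/Reimbursement is broken.* It says "Caregivers who do not receive LNS-LQ supplementation for their child during the study will still receive the same opportunities for medical review". Four scheduled reviews in each group can satisfy it, so no clear contradiction exists.
- *The data safety monitoring board would see a false harm signal.* The board is to receive fatality reports, serious adverse events and reasons for termination, and its one stopping rule concerns mortality. Deaths and hospital admissions are unlikely to be missed through a four-week gap between visits.

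What the reply does not remove is the open rule on adverse events. Nothing exempts reports made at weeks 6 and 10, and neither the calls nor the book is arranged to fill the reference group's gap. Nor can the SAP repair it alone: analysis cannot recover illness never asked about, or set aside restocking reports whose source was not recorded.

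**Conclusion.** The point holds as an ascertainment asymmetry that the plan permits, not as unequal counting that it prescribes. It concerns illness episodes and non-serious adverse events in any supplemented versus unsupplemented comparison. The factorial contrasts among arms A to D are untouched, because those arms share one schedule.

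The ratio of time covered lies between 1.0 and 1.5, and the protocol does not show where. A reader might take 1.5 as the expected inflation. The documents do not support that: it needs full capture of illness at weeks 6 and 10, recall of two weeks or less, and no help from phone calls or the exercise book, none of which is stated. The case for acting is that the remedy is cheap and missed illness history cannot be recovered later.

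**What to change.** Either change is enough.

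1. **Common contacts only.** For supplemented versus reference, count morbidity and adverse events from weeks 2, 4, 8 and 12. At each, ask every caregiver about the whole time since the previous common visit, which gives 2 + 2 + 4 + 4 = 12 weeks in both groups. Record the source of each report and list week 6 and 10 reports separately. The cost is protocol and SOP wording plus a source field. Events that surface only at weeks 6 and 10 leave this comparison but stay in the safety listings.

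2. **Matched contact.** Fix two of the already planned phone calls at weeks 6 and 10 for reference families, and put the same short illness questions to supplemented families at those weeks. The cost is at most 150 × 2 = 300 short calls, plus the brief questions to supplemented families. Staff other than the distributors should ask them, since distributors are kept out of clinic data. Blinded clinic staff should not make the calls, because a call meant only for reference families reveals the allocation.

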**Inclusion**

**12 wks/ Discharge**

E. Reference n= 150

Children HAZ <-2

N = 750

A. LNS-LQ n= 150

B. LNS-LQ n= 150

C. LNS-LQ n= 150

D. LNS-LQ n= 150

**Figure 2: MAGNUS study design framework.** 750 children with HAZ <-2 are included and randomised to one of four supplements or to a reference group. LNS-LQ is allocated for a fixed duration of 12 weeks after inclusion.. The reference group is not supplemented. LNS-LQ: Large-quantity lipid-Based Nutrient Supplement. HAZ: Height-for-age Z score

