### Random allocation

Thereafter, caregivers are informed of allocation to supplementation or the reference group. Those not allocated to supplementation are given a token of appreciation (given at each follow-up clinic visit), valued at around 5000 UGX but not more than 10 000UGX, for example clothes soap. If allocated to LNS caregivers are given training concerning appropriate use of LNS before they are allocated a two week supply. Prior to departure all caregivers are given a follow-up plan. Refer to the SOP for further details.

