## Dosage

Children randomised to LNS will be allocated one 100g sachet of LNS-LQ (530-535kcal) per day for 12 weeks.

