# Schedule of measurements and assessment

**
[figure not shown]
**

**
[figure not shown]
Figure 4: MAGMAM data collection time-points and visits.**

Timeline for enrolment, interventions, assessments and visits for each participant enrolled in the study. Phone follow-up and home visits are unfixed time points depending on need and availability. Time points are considered valid if taken within ±7 days of baseline, week 2 and week 4 and ±14 days from all other time points.

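### The week-12 validity window lets the only post-baseline blood and stool samples be taken up to 14 days after LNS supply ends, which may dilute some tertiary biomarker contrasts

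*Protocol*

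**What the plan says.** **Supply.** Section 12 of the Protocol (Dosage) allocates "one 100g sachet of LNS-LQ (530-535kcal) per day for 12 weeks". The summary, under Figure 2, adds "Supplemented children are provided one LNS-LQ sachet per day (in two-week allocations) over a period of 12 weeks". Caregivers are trained at inclusion "before they are allocated a two week supply" (Random allocation), and the Figure 2 legend in section 10 states "LNS-LQ is allocated for a fixed duration of 12 weeks after inclusion".

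**Visits.** All children are asked to "return to a specific study site for a follow-up visit at 2, 4, 8 and 12 weeks post inclusion" (Follow-up clinic visits). The same section adds: "Those receiving LNS are also requested to return at 6 and 10 weeks post inclusion to restock sachets". No allocation is described at or after week 12.

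**Samples.** Blood and stool are collected at baseline and at week 12 only (Follow-up clinic visits; section 22, Sample collection and storage, and Table 2). Stool may be collected at home with a kit.

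**Window.** The Figure 4 legend in section 19 gives baseline, week 2 and week 4 a validity window of 7 days either side "and ±14 days from all other time points". Week 12 is one of those others. The text shown gives no separate window for samples.

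**Rationale.** The Background says milk proteins are thought to act by stimulating IGF-1 and insulin, and that whey permeate, being mostly lactose, may have a prebiotic effect on intestinal bacteria.

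**The concern.** The supply rule and the sampling rule were set separately. Supply is fixed in time from inclusion, while the final sample may follow the end of supply by as much as one whole lot. A child sampled in that interval is eating the family diet, as the reference group does, yet contributes a week-12 value to a supplemented arm.

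This need not matter much for attained length, which largely retains what was gained. It could matter for a marker that tracks current intake. The whey permeate comparison is essentially a lactose comparison: Table 1 gives 15.7 and 15.3 g per sachet with permeate, against 0.4 and 0 g without. That contrast ends with the last sachet. With no earlier post-baseline sample, nothing in the data can stand in for a late one.

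At stake is the reading of the mechanistic outcomes listed as tertiary in section 17: IGF-1, insulin, citrulline, the stool markers and the microbiota. A null result could be taken as absence of effect when part of it is time off product. Children who used every sachet on schedule run out first, so among children sampled late the best adherers have the longest gap.

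**Working it through.** **1. End of supply.** Lots are issued at weeks 0, 2, 4, 6, 8 and 10, with 14 sachets each: 6 × 14 = 84 sachets. The last restock is on day 70, and 70 + 14 = day 84. This reproduces the protocol's stated 12 weeks.

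**2. Validity window for week 12.** 84 − 14 = day 70 to 84 + 14 = day 98.

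**3. Days off product** = max(0, sample day − last supply day).

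| Sample day | Full attendance, one sachet per day | Week-10 restock missed (supply ends day 70) |
|---|---|---|
| 70 | 0 | 0 |
| 77 | 0 | 7 |
| 84 | 0 | 14 |
| 91 | 7 | 21 |
| 98 | 14 | 28 |

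The last column reflects non-adherence and is shown only for range.

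**4. Leftover sachets (assumption).** If a share m of daily sachets is missed and eaten later at one per day, the last sachet falls at about day 84/(1 − m). For m = 5%, 10% and 15% this is day 88, 93 and 99, so the gap at day 98 shrinks to about 10, 5 and 0 days.

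**5. Illustration of dilution (assumptions only).** The documents give neither the speed at which any marker reverts nor the share of samples taken late. Suppose an effect decays exponentially with half-time h after the last sachet, so k = ln 2/h. Suppose also that a fraction f of samples is late, spread evenly over D days. The mean effect left among late samples is r = (1 − exp(−kD))/(kD). The overall effect is 1 − f(1 − r) of its on-product size, and the sample size needed to compensate rises by 1/(overall effect)².

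| Half-time | Left at day +14 | r, D = 14 | f = 20%, D = 14 | Sample-size factor | f = 50%, D = 14 | f = 20%, D = 3 |
|---|---|---|---|---|---|---|
| 1 day | 0.01% | 0.103 | 82% | 1.49 | 55% | 88% |
| 3 days | 4% | 0.297 | 86% | 1.35 | 65% | 94% |
| 7 days | 25% | 0.541 | 91% | 1.21 | 77% | 97% |

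Worked row, h = 1 day: kD = 0.693 × 14 = 9.70; r = 1/9.70 = 0.103; 1 − 0.2 × 0.897 = 0.82; 1/0.82² = 1.49. The result is driven by f, D and h, none of which is in the protocol.

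**The case against.** **A window this wide is a feasibility choice, and the protocol works against lateness.** It provides phone reminders, home visits for missed appointments and travel reimbursement. This stands as a reason to expect a typical gap well below 14 days. It does not close the gap, because none of these measures sets a time limit.

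**The mechanism is not quantified.** No section says how quickly IGF-1, insulin, citrulline or the microbiota would revert. This stands. A reader might infer that late samples pull every biomarker contrast towards zero, or that the trial would lose 9% to 45% of its biomarker effect. The documents support neither. For ferritin, transferrin receptor, the vitamins, CRP and AGP they give no ground for rapid reversion, and the percentages follow from assumed inputs.

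**The full 14 days needs near-complete adherence and a maximally late visit.** This also stands. Households with other young children receive extra sachets, which may lengthen actual use further.

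**There is no contradiction.** A reader might infer that the protocol promises on-treatment values and then breaks the promise. It does not: section 17 defines outcomes as measured from baseline to 12 weeks. This is a design weakness, not an inconsistency, and it does not reach the primary outcomes.

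**Some of this may sit elsewhere.** Analysis detail is left to an analysis plan, stool instructions to an SOP, and the Figure 4 image is not shown. Distribution logs and returned empty sachets could approximate the last-sachet date. The absence of a sensitivity analysis is therefore not a fault of the protocol. Visit targets and recorded dates, however, have to be settled before data collection, because an analysis plan cannot recover a date that was never recorded.

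**Conclusion.** The mismatch is real and exact on the text: supply ends at about day 84, and the only post-baseline blood and stool samples are accepted to day 98. Some tertiary biomarker samples may therefore be taken up to 14 days after a fully adherent child's last sachet.

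The consequence is conditional. Dilution occurs only for a marker that reverts after intake stops, and only to the extent that samples are late. The protocol's intake-based rationale makes this plausible for IGF-1, insulin and a lactose effect on the microbiota; for citrulline and the stool markers it is a possibility. The size cannot be computed from the documents, so the dilution table is illustration, not an estimate. The point is a cheap improvement affecting tertiary outcomes.

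**What to change.** In section 19 of the Protocol:

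- Set a target for week-12 blood and stool, including home stool kits, at or just before the end of the last two-week lot. Keep the present 14-day window as the validity rule and for anthropometry. A hard cut-off at day 84 is not advised: one visit carries all week-12 assessments, and a child one day late would fall outside it.
- Record on the CRF the date of the last sachet and the actual date of each sample.
- Keep all samples in the intention-to-treat analysis. Pre-specify a supportive biomarker analysis, either restricted to samples taken while on product or, within the supplemented arms, adjusted for days since last sachet. The reference group has no last sachet, so the adjusted form cannot serve the LNS-versus-reference comparison. Time off product arises after randomisation and depends partly on adherence, so this analysis supports the main one and does not replace it.

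The cost is slightly less scheduling slack for the final visit, the added CRF date fields and one extra analysis. No change to product supply is involved.
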